## Abstract

**Background:**

Chronic obstructive pulmonary disease (COPD) is the fifth leading cause of death in China with a reported prevalence of 8.2% people aged ≥40 years. It is recommended that Chinese physicians follow Global Initiative for Chronic Obstructive Lung Disease (GOLD) and national guidelines, yet many patients with COPD in China remain undiagnosed. Furthermore, missed diagnoses and a lack of standardized diagnosis and treatment remain significant problems. The situation is further complicated by a lack of large-scale, long-term, prospective studies of real-world outcomes, including exacerbation rates, disease severity, efficacy of treatment, and compliance of COPD patients in China.

**Methods/design:**

The REALizing and improving management of stable COPD in China (REAL) study is a 52-week multi-center, prospective, observational trial. REAL aims to recruit approximately 5000 outpatients aged ≥40 years with a clinical diagnosis of COPD per GOLD 2016. Outpatients will be consecutively recruited from approximately 50 tertiary and secondary hospitals randomly selected across six geographic regions to provide a representative population. Patients will receive conventional medical care as determined by their treating physicians.

The primary objective is to evaluate COPD patient outcomes including lung function, health status, exacerbations, hospitalization rate, and dyspnea following 1 year of current clinical practice. Secondary objectives are to assess disease severity, treatment patterns, adherence to medication, and associated risk factors. Data will be collected at two study visits, at patients’ usual care visits, and by telephone interview every 3 months.

**Discussion:**

Knowledge of COPD among physicians in China is poor. The REAL study will provide reliable information on COPD management, outcomes, and risk factors that may help improve the standard of care in China. Patient recruitment began on 30 June 2017 and the estimated primary completion date is 30 July 2019.

**Trial registration:**

ClinicalTrials.gov identifier: NCT03131362. Registered on 20 March 2017.

## Background

Chronic obstructive pulmonary disease (COPD) is characterized by persistent respiratory symptoms and airflow limitation that is due to airway and/or alveolar abnormalities usually caused by significant exposure to noxious particles or gases [1]. Despite being a common, preventable, and treatable disease [1], COPD is the fifth leading cause of death in China [2]. The prevalence of COPD varies among geographic regions of China between 5 and 13% [3], with a reported prevalence of 8.2% among people aged ≥40 years [4].

The Chinese Thoracic Society recommends [5] that physicians follow Global Initiative for Chronic Obstructive Lung Disease (GOLD) [6] and national guidelines [5], yet adherence to guidelines among Chinese physicians is low [7]. Knowledge of COPD among Chinese physicians, including respiratory specialists, can be poor [8]. For instance, almost a quarter (22.1%) of respiratory physicians surveyed did not consider smoking to be the most significant risk factor for the development of COPD [8]. Furthermore, despite several large studies conducted over the last 10 years implicating biomass fuel as an important risk factor among Chinese patients with COPD [4, 9, 10], only 20.8% of respiratory physicians surveyed believe biomass fuel plays a critical role [8].

An observational study of respiratory diseases in the Asia-Pacific region included 210 patients with COPD from Taiwan but did not include patients from mainland China [11, 12]. Of these Taiwanese patients, the mean age was 71 and most (85.2%) were retired, there was a high proportion (78.6%) of “ever smokers”, but only 18.8% were current smokers [12]. Medication use was high (91.9%) in the preceding 4 weeks with mucolytics (44.8%) and methylxanthines (43.3%), the most frequently prescribed therapy, and direct medical costs were high (82.8% of direct costs) [12]. A recent study revealed that just over a quarter (26%) of newly diagnosed COPD patients surveyed in four major Chinese cities did not use any pharmacological treatment [13].

Many patients with COPD remain undiagnosed in China [4]. Raising awareness of COPD is the first step to improving rates of diagnosis, yet large-scale studies of real-world outcomes, exacerbation rates, and disease severity of COPD patients in China are lacking. Furthermore, there is a paucity of data derived from large Chinese cohorts regarding COPD maintenance and exacerbation treatment patterns, non-pharmacological management and risk factors for exacerbations, disease severity, and adherence.

The REALizing and improving management of stable COPD in China (REAL) trial aims to provide reliable information on COPD management, outcomes, and risk factors in China. Here we describe the rationale and design of this 52-week multi-center, prospective, observational study (NCT03131362, registered on 20 March 2017; protocol version 1.0, 9 July 2016). The primary objective is to evaluate COPD patient outcomes (including exacerbations) following 1 year of current clinical practice. Secondary objectives are to assess disease severity, treatment patterns, adherence to medication, and investigate associated risk factors. Clinical assessments will include spirometry, bronchial dilation and induced sputum tests, fractional exhaled nitric oxide (FENO), and chest computed tomography (CT) imaging. Patient reported outcomes will include the COPD Assessment Test (CAT) [14], modified Medical Research Council (mMRC) questionnaire [15] and COPD knowledge questionnaire (COPD-Q) [16]. Data on medication type, adherence, non-drug therapies, and total COPD treatment costs will also be collected.

## Methods/design

### Site selection

Patient recruitment began in June 2017 and the estimated primary completion date is 30 April 2019. To provide a representative population of Chinese patients with COPD, REAL aims to recruit approximately 5000 patients from approximately 50 tertiary and secondary hospitals across six geographic regions (north, northeast, east, south central, southwest, and northwest). A multi-stage, stratified, and cluster sampling method will be used to select a nationally representative sample of hospitals with respiratory departments (Fig. 1). Initially, 125 tertiary and 125 secondary hospitals administered by the National Health and Family Planning Commission (NHFPC) will be randomly selected from the six geographic regions. From this list, 25 tertiary and 25 secondary hospitals will be further selected based on their willingness and capacity to participate, and the suitability of the primary investigator. If the first round of sampling fails to yield enough sites, alternative hospitals will be selected by random selection of other sites in cities where hospitals declined to participate or further random sampling of the region.

**Fig. 1 Fig1:**
[figure not shown]
Multi-stage, stratified, cluster sampling method. * All secondary and tertiary hospitals administered by NHFPC. ^†^ Excluding traditional Chinese medicine hospitals; the actual hospital number and the ratio of tertiary to secondary hospitals in each region may be adjusted based on the hospital distribution in the region; subject numbers may be adjusted according to COPD outpatient numbers at the site

### Patients

Eligible patients will be consecutively screened and enrolled in the study when they routinely visit their physician at a participating site between June 2017 and April 2018. Patients will be eligible for inclusion if they are outpatients aged ≥40 years, with a clinical diagnosis of COPD per GOLD 2016 [17]. The study will be performed in accordance with the Declaration of Helsinki and good clinical practice; as such, signed and dated informed consent will be obtained from every patient prior to participating in the study (see Additional file 1: Subject information and consent form). Exclusion criteria include participation in any interventional studies in the 30 days prior to enrollment and an acute exacerbation of COPD in the previous 4 weeks.

### Data collection

There will be two prespecified study-specific visits at baseline (V0) and 12 months thereafter (V1). Telephone contact (TC) follow-ups will be arranged every 3 months following V0 (three TC follow-ups in total), during which investigators will call participants and gather study information (Fig. 2). Demographic data and baseline characteristics will be collected using case report forms (CRF) at V0. At V0, V1, and all TC follow-ups, symptoms, drug treatment, non-drug treatment, exacerbations, other respiratory diseases, comorbidities, complications, and direct cost will be collected from CRF and patient-reported outcome (PRO) questionnaires (mMRC and CAT) will be completed by the patient with minimal input from the investigator before any other procedures (questionnaires and stamped addressed envelopes will be provided in advance of TC follow-ups and investigators will remind participants to complete and return them during the call). If available at study visits, spirometry, chest CT imaging, induced sputum, and lab test data will be collected. With the exception of PRO, all the above study data will also be collected during patient’s usual care (UC) visits if available. Table 1 presents the Standard Protocol Items: Recommendations for Interventional Trials (SPIRIT) [18] figure for the REAL study (see also Additional file 2: SPIRIT checklist).

**Fig. 2 Fig2:**
[figure not shown]
Study flow chart

**Table 1 Tab1:** Standard Protocol Items: Recommendations for Interventional Trials (SPIRIT) figure for the REAL study

Month	Enrollment	Data collection				
	0	3 ± 1	6 ± 1	9 ± 1	/	12 ± 1
Visit	V0	TC1	TC2	TC3	UC	V1
Informed consent	X					
Inclusion/exclusion criteria	X					
Demography (date of birth, ethnicity, gender, education, marital status, socioeconomic status, insurance status, residence area, occupation)	X					
Physical examination	X					X
Smoking history	X					
COPD history	X					
Disease severity GOLD 2016	X					X
Comorbidities, other respiratory diseases	X	X	X	X	X	X
Exacerbations	X	X	X	X	X	X
Symptoms	X	X	X	X	X	X
Spirometry and bronchial dilation if available	X				X	X
CAT, mMRC	X	X	X	X		X
COPD-Q	X					X
FENO if available	X				X	X
Chest CT imaging if available	X				X	X
Induced sputum test if available	X				X	X
Lab tests (blood gases, C-reactive protein and hematology) if available	X				X	X
COPD medications	X	X	X	X	X	X
COPD non-pharmacological treatment	X	X	X	X	X	X
Total COPD treatment expenses	X	X	X	X	X	X

### Endpoints

Disease severity will be measured by airway limitation (post-bronchodilator forced expiratory volume in 1 s, FEV_1_) and assessment of symptoms/risk of exacerbations (A/B/C/D) [17]. Exacerbations will be classified as mild: requiring an increase in rescue medication ≥3 puffs/day for ≥2 consecutive days; moderate: requiring systemic glucocorticosteroids and/or antibiotics; or severe: hospitalization, emergency room visit, or leading to death [19]. Endpoints are given in Table 2.

**Table 2 Tab2:** Endpoints of REAL

Endpoints	Outcome measures
Primary	Mean rate of acute exacerbations (per patient per year)^a^ Proportion of patients hospitalized due to exacerbation^a^ Distribution of COPD exacerbations by severity Mean reduction from baseline of available FEV_1_^a^ Mean change in CAT total score Mean change in mMRC score Mean change in COPD-Q total score
Secondary	Distribution of disease severity at baseline and V1 Distribution of COPD medication by drug class^b^ at baseline and V1 Distribution of maintenance medication^a^ and dosage by disease severity at baseline and V1 Distribution of maintenance medication^b^ at each usual visit Distribution of medications for exacerbations Distribution of non-drug treatments (health education, smoking cessation, physical activity, and vaccination) Medication compliance Visit compliance Mean total direct cost of COPD management over 1 year
Exploratory	Risk factors for exacerbations Risk factors for disease severity Risk factors for medication compliance

^a^ Also stratified by disease severity at baseline

^b^*ICS* Inhaled corticosteroid, *LABA* long-acting β_2_-agonist, *ICS/LABA* combined long-acting β_2_-agonists plus corticosteroid, *SABA* short-acting β_2_-agonist, *SAMA* short-acting muscarinic antagonist, *SABA/SAMA* combined short-acting β_2_-agonist plus short-acting muscarinic antagonist, *LAMA* long-acting muscarinic antagonist, methylxanthines, mucolytics, traditional Chinese medicine, and others (antibiotics, systemic corticosteroids, vaccines, antioxidant agents, etc.)

### Sample size estimate

Assuming the exacerbation rate is 1.5 per person per year, 3500 subjects will enable a predefined limit of precision of 0.041 (half the width of 95% confidence interval [CI]). Based on a 30% patient drop-out rate, overall 5000 subjects will be required.

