### Statistical analysis

As an observational study, there will be no pre-planned hypothesis testing, and data analysis will be primarily descriptive in nature. Summary statistics will be presented for both primary and secondary endpoints. For continuous variables, these will include the number, mean, median, standard deviation (SD), minimum values, and maximum values. For categorical variables, these will include frequency counts and percentages for each category. The rate of exacerbations per year will be estimated under the assumption of Poisson distribution. The mean and standard error of the overall exacerbation rate per year will be presented. To reduce any potential regional bias, stratified and weighted summaries will be calculated using the proportions of the regional and total populations if applicable. A similar approach may also be applied with respect to sites. COPD treatments will be summarized by drug class and by treatment summaries may be performed. Risk factors for exacerbations, disease severity, and medication compliance will be analyzed using Poisson regression and multinomial regression and presented as odds ratios and 95% CI.

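### The planned half-width of 0.041 assumes 3500 independent patients, although they come from a cluster sample of about 50 hospitals; it holds only if the within-hospital correlation is essentially zero

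*Protocol article*

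**What the plan says.** The Sample size estimate section starts from a single rate, "Assuming the exacerbation rate is 1.5 per person per year", and concludes that "3500 subjects will enable a predefined limit of precision of 0.041 (half the width of 95% confidence interval [CI". It then allows for attrition: "Based on a 30% patient drop-out rate, overall 5000 subjects will be required". No ICC, design effect or overdispersion term appears.

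The Site selection section sets out how patients are reached: "A multi-stage, stratified, and cluster sampling method will be used to select a nationally representative sample of hospitals with respiratory departments". The target is about 5000 patients from about 50 hospitals, half tertiary and half secondary, in six regions.

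The Statistical analysis section plans no hypothesis test. For the exacerbation rate it says "The rate of exacerbations per year will be estimated under the assumption of Poisson distribution" and "The mean and standard error of the overall exacerbation rate per year will be presented". It adds weighted and stratified summaries by region where applicable, and says that something similar may be done for sites. It does not say how the standard error will treat patients from the same hospital.

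**The concern.** The precision statement and the sampling design do not match. A half-width that depends only on the rate and the number of patients belongs to a simple random sample. Here patients are recruited consecutively within about 50 hospitals, and the article gives reasons to expect exacerbation counts to be alike within a hospital:

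- The Endpoints section defines moderate exacerbations by use of systemic steroids or antibiotics, and severe ones by admission, emergency visit or death. Counts therefore depend partly on local prescribing and admission practice.
- The Discussion notes that more than half of exacerbations may go unreported and relies on calls by investigators to find them. Ascertainment therefore depends partly on site staff.

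With no hypothesis test, this half-width is the only quantitative justification for the sample size, and the exacerbation rate is the first primary endpoint listed. If the hospitals differ, a correctly computed interval will be wider than planned. If the standard error were computed as the sample size implies, the interval would be too narrow.

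**Working it through.** **Inputs from the article.** Rate 1.5 per person per year, 3500 evaluable patients, two-sided 95% interval, 30% drop-out, 5000 enrolled (Sample size estimate); Poisson distribution (Statistical analysis); about 50 hospitals (Site selection); 52 weeks of follow-up, so one person-year per completer (Abstract).

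**Step 1: reproduce the plan's figures.**

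- Half-width = 1.96 × √(1.5/3500) = 0.0406, which rounds to 0.041.
- Enrolment = 3500/0.70 = 5000.

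Both agree. The stated precision is therefore the independent-patient figure, with design effect 1 and variance equal to the mean.

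**Step 2: cluster size.** m = 3500/50 = 70 evaluable patients per hospital, taken as equal.

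**Step 3: add clustering.** Design effect DE = 1 + (m − 1) × ICC = 1 + 69 × ICC; half-width = 1.96 × √(1.5 × DE/3500); effective n = 3500/DE. The ICC is not in the document, so the values below are assumptions.

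| Assumed ICC | DE | Half-width | Effective n |
|---|---|---|---|
| 0.001 | 1.069 | 0.042 | 3274 |
| 0.005 | 1.345 | 0.047 | 2602 |
| 0.01 | 1.69 | 0.053 | 2071 |
| 0.02 | 2.38 | 0.063 | 1471 |
| 0.05 | 4.45 | 0.086 | 787 |

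**Step 4: the break-even ICC.** The half-width reaches 0.0415 when DE = (0.0415/0.0406)², or about 1.046 with unrounded figures. That gives ICC = 0.046/69, about 0.0007.

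**Step 5: the same check through variation between hospitals.** With a between-hospital SD s in the true rate, half-width = 1.96 × √(s²/50 + 1.5/3500), and ICC = s²/(s² + 1.5).

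- s = 0.15 (10% of 1.5): ICC about 0.015, half-width 0.058. The hospital term alone gives 1.96 × 0.15/√50 = 0.042, so with 50 hospitals no number of patients per hospital would bring it lower.
- s = 0.2: ICC about 0.026, half-width 0.069.
- s = 0.3: ICC about 0.057, half-width 0.093.

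**Step 6: if clustering were ignored in the reported interval.** Actual coverage of a nominal 95% interval is about 2Φ(1.96/√DE) − 1. At ICC 0.02 this is 2Φ(1.27) − 1, about 80%; at ICC 0.05 it is 2Φ(0.93) − 1, about 65%.

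**Step 7: the other assumption in 0.041.** Variance equal to the mean excludes overdispersion between patients. As an illustration without clustering, an assumed negative binomial dispersion of 0.5 gives variance 1.5 + 0.5 × 1.5² = 2.625 and half-width 1.96 × √(2.625/3500) = 0.054.

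**The case against.** The strongest reply has several parts.

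- **The arithmetic is right.** This stands. A reader might infer a calculation error or a wrong N; both figures reproduce. The fault is the independence assumption set against the article's own sampling design.
- **The size of the shortfall is not in the document.** This also stands. A reader might infer that the design is shown to miss 0.041 by a wide margin. At ICC 0.001 the half-width is 0.042, close to plan. Only the direction is established.
- **The study is descriptive and nothing is decided on 0.041.** True, and even 0.086 is 5.7% of 1.5, so the study remains informative. But a stated precision that justifies the sample size should be one that the design can deliver.
- **An analysis plan that is not shown may use a clustered variance.** It may, and the article does not say that standard errors will ignore sites. A reader might infer that the published interval will be falsely narrow; that is a risk, not something the text commits to. A clustered variance would correct the reported interval, but it would not restore the planned 0.041.
- **The site-level approach already covers this.** It does not. It is optional, and weighting changes the point estimate without making the variance allow for correlation.
- **Stratification could recover precision.** Some, because only hospital variation within strata should then count. In the other direction, the note to Fig. 1 lets subject numbers follow outpatient volume, and unequal sites and regional weights usually cost precision.

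Two further inferences are not supported. One is that every other endpoint has the same defect: for the remaining primary and secondary endpoints the Statistical analysis section lists only descriptive summaries, with no stated precision or interval to miss. The other is that season drives the correlation: each completer is followed for 52 weeks and so passes through all seasons.

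**Conclusion.** The point holds in this form: 0.041 is the half-width for 3500 independent patients with Poisson variance, and the described design of about 50 hospitals with about 70 evaluable patients each delivers it only if the hospital ICC is essentially zero (below about 0.0007). For assumed ICCs of 0.01 to 0.05 the half-width is 0.053 to 0.086, or 1.3 to 2.1 times the stated value; at 0.001 to 0.005 it is 0.042 to 0.047.

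These sizes rest on equal hospital sizes, 30% drop-out as planned, a total variance of 1.5, and no credit or penalty for stratification and weighting. They also take the hospital as the cluster, which is how the text describes selection. The stated precision should be corrected. Nothing here puts the 5000 enrolment target or the value of the study in doubt.

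**What to change.** 1. **Sample size estimate.** Keep N = 5000. State an assumed ICC range with its design effect and the resulting half-width, for example about 0.042 to 0.086 for ICC 0.001 to 0.05 with 70 evaluable patients per hospital. Say that 0.041 holds only under independence and variance equal to the mean.
2. **Statistical analysis.** State that the standard error and 95% interval of the exacerbation rate use a variance clustered on hospital, for example a sandwich or GEE estimator with degrees of freedom based on the number of sites, whether or not regional or site weights are applied. Describe this as cluster-robust rather than strictly design-based: the final hospitals are chosen partly on willingness, capacity and suitability of the investigator, so their inclusion probabilities are not known.

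Restoring 0.041 by enlarging the study is not proposed. At ICC 0.01 and 70 evaluable per hospital it would take 3500 × 1.69 = 5915 evaluable patients, 5915/0.70 = 8450 enrolled, and about 85 hospitals. The recommended change costs a less favourable stated precision and minor analysis code, with no extra patients.

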### Safety assessments

As a non-interventional study with no specific AstraZeneca drug under investigation, there will be no proactive safety data collection. Any adverse events considered related to any AstraZeneca products will be reported to health authorities as per local regulations and to the AstraZeneca China patient safety group.

### Statistical analysis

As an observational study, there will be no pre-planned hypothesis testing, and data analysis will be primarily descriptive in nature. Summary statistics will be presented for both primary and secondary endpoints. For continuous variables, these will include the number, mean, median, standard deviation (SD), minimum values, and maximum values. For categorical variables, these will include frequency counts and percentages for each category. The rate of exacerbations per year will be estimated under the assumption of Poisson distribution. The mean and standard error of the overall exacerbation rate per year will be presented. To reduce any potential regional bias, stratified and weighted summaries will be calculated using the proportions of the regional and total populations if applicable. A similar approach may also be applied with respect to sites. COPD treatments will be summarized by drug class and by treatment summaries may be performed. Risk factors for exacerbations, disease severity, and medication compliance will be analyzed using Poisson regression and multinomial regression and presented as odds ratios and 95% CI.

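### The overall exacerbation rate, its standard error and the planned precision of 0.041 assume Poisson variance, although the plan expects rates to differ between patients, so that standard error will be too small

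*Protocol article*

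**What the plan says.** The Statistical analysis section of the protocol article fixes the distribution for the exacerbation rate: "The rate of exacerbations per year will be estimated under the assumption of Poisson distribution". It continues: "The mean and standard error of the overall exacerbation rate per year will be presented". The same section names Poisson regression, with 95% confidence intervals, among the models for risk factors. It also provides for regional and possibly site weighting, which it presents as a way to reduce bias, not as a correction of the variance.

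The Sample size estimate section gives the precision: "Assuming the exacerbation rate is 1.5 per person per year, 3500 subjects will enable a predefined limit of precision of 0.041", defined as half the width of a 95% confidence interval. It then allows for dropout: "Based on a 30% patient drop-out rate, overall 5000 subjects will be required".

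The Endpoints section describes patients who are not alike in exacerbation risk. Disease severity includes an "assessment of symptoms/risk of exacerbations (A/B/C/D" grading. In Table 2 the exacerbation rate carries the footnote "Also stratified by disease severity at baseline", and risk factors for exacerbations are an exploratory endpoint.

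**The concern.** When a single overall rate is estimated, the Poisson standard error is right only if all patients share one underlying rate. The counts then have a variance equal to their mean. If patients differ, the pooled counts are a mixture of Poisson distributions with a larger variance. This happens even within one hospital, so it is a separate matter from correlation between patients of the same site.

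The Endpoints section is built on the expectation that patients differ. The Statistical analysis and Sample size estimate sections assume, for the overall rate, that they do not.

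At stake is the stated uncertainty of the first-listed primary endpoint, which is also the one that sizes the study. The study plans no hypothesis tests, so the precision of its estimates is its main inferential output. An interval that is too narrow would overstate how well the national rate is known.

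**Working it through.** **Inputs from the protocol article.** Rate 1.5 per person per year, 3500 evaluable patients, two-sided 95% interval with half-width 0.041, and 30% dropout (Sample size estimate); Poisson distribution (Statistical analysis). One year of follow-up per evaluable patient is taken from the 52-week design.

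**Input not in the documents.** The spread of individual rates. It is assumed below and shown over a range.

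**Step 1: reproduce the plan's figure.**
- Poisson SE = √(1.5/3500) = 0.0207.
- Half-width = 1.96 × 0.0207 = 0.0406, which rounds to the stated 0.041.
- Enrolment = 3500/(1 − 0.30) = 5000, as stated.

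The arithmetic is correct. It also shows that the planned precision uses variance = mean, with no allowance for variation between patients.

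**Step 2: let rates differ between patients.** If individual rates vary around 1.5, the variance of a one-year count is 1.5 + Var(rate). This exceeds 1.5 whenever Var(rate) is above zero, so the direction is certain. The mean count per patient-year is still 1.5, so the point estimate is not biased.

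**Step 3: size under assumed gamma-distributed rates with shape k.**
- Variance = 1.5 + 1.5²/k
- SE ratio r = √(variance/1.5)
- Half-width = 1.96 × √(variance/3500)
- Actual coverage of a nominal 95% Poisson interval = 2Φ(1.96/r) − 1

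| k (assumed) | Variance | True SE | r | Half-width | Coverage |
|---|---|---|---|---|---|
| no variation | 1.50 | 0.0207 | 1.00 | 0.041 | 95% |
| 4 | 2.06 | 0.0243 | 1.17 | 0.048 | 90.5% |
| 2 | 2.63 | 0.0274 | 1.32 | 0.054 | 86% |
| 1 | 3.75 | 0.0327 | 1.58 | 0.064 | 79% |
| 0.5 | 6.00 | 0.0414 | 2.00 | 0.081 | 67% |

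**Step 4: a simple illustration (assumed).** Take two equal groups with rates 0.75 and 2.25. Then Var(rate) = 0.75² = 0.5625, the total variance is 2.0625, and r = √(2.0625/1.5) = 1.173. The true SE is 17% larger than the Poisson SE; put the other way, the Poisson SE is 1 − 1/1.173, or about 15%, too small.

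**Step 5: the risk-factor regression.** A simulation used 4000 null data sets per k, 1750 patients per group, and a Poisson Wald test of one binary factor with no other covariates. It gave false-positive rates of 13%, 21% and 32% for k = 2, 1 and 0.5, against a nominal 5%. All heterogeneity is left unexplained in that model, so for each k these are upper illustrations and not forecasts for the planned analysis.

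**The case against.** **A condensed article may leave the variance estimator to the analysis plan.** A scale parameter or robust variance would be compatible with naming Poisson, and so would an ordinary standard error computed from the sample standard deviation. This stands as a caution: the unseen plan may already contain the remedy. It does not remove the point. The article states the distributional assumption for the rate, reports the standard error directly after it, and derives 0.041 from the same variance. The fault lies in a stated choice, not in an omitted detail.

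**The evidence of heterogeneity bears on the overall rate, not automatically on the strata or the regression.** This stands. Poisson regression requires variance = mean only given the covariates, and differences between severity strata do not affect the standard error within a stratum. In the two-group example, the excess variance disappears once the grouping is a stratum or a covariate. A reader might infer that every stratum-specific interval and every risk-factor interval will be too narrow, and that chance associations will be reported as risk factors. The documents do not support that. It would require residual variation of unknown size, and for the last part a reporting rule based on significance, which the article does not contain.

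**The study is descriptive and large.** This also stands as a limit on weight. The article disclaims pre-planned hypothesis tests, and risk factors are exploratory. Even at k = 0.5 the half-width is 0.081, or 0.081/1.5 = 5.4% of the rate. A reader might also infer that enrolment must rise. Holding 0.041 would take 1.96² × variance/0.041², which is 4714 to 13,712 evaluable patients over the assumed range. But no decision in the article depends on reaching 0.041, and the dispersion is unknown, so a larger sample does not follow.

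**Conclusion.** The point holds for the overall exacerbation rate. A standard error computed under the stated Poisson assumption will be too small if patients' rates differ, as the Endpoints section expects, and 0.041 is attainable only if they do not.

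The direction follows from the variance identity. The size rests on assumed dispersion: over gamma shapes from 4 to 0.5, the true standard error is 1.17 to 2.0 times the Poisson one, with one year of follow-up for each of 3500 patients and before any effect of hospital clustering.

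For the severity strata and the exploratory risk-factor model the conclusion is conditional: standard errors and intervals are too narrow only as far as strata or covariates leave variation unexplained. The estimated rate is not biased, and the plan's sample-size arithmetic is correct on its own assumption.

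**What to change.** **Statistical analysis.** Estimate the exacerbation rate and the exacerbation risk-factor model by negative binomial regression with log follow-up time as offset. Alternatively, keep the Poisson mean model and use a robust (sandwich) variance. Clustering that variance by hospital is preferable, because it also covers correlation within the roughly 50 sites, which a patient-level negative binomial model would leave uncorrected. In either case, report the dispersion estimate beside the rate.

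**Sample size estimate.** State that 0.041 holds only without overdispersion, and show the half-width over a range of dispersion, for example 0.048 to 0.081 for the shapes used above. Leave the sample size as it is.

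**Cost.** A change of model or variance option, and a sentence or two in each of the two sections. No new data are needed. The price is wider reported intervals.
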